## 6.2 RANDOMISATION

Study patients will be randomly allocated to NO or standard care, and stratified by age group (<42 days, 42 days -24 months) and uni-versus biventricular lesions for each site. Randomisation will be done by using REDCap randomisation. For incomplete data or withdrawal of consent the intention to treat principle will be applied.

Stratification

- age group (0 to <42 days and 42 days to 2 years)
- uni-versus biventricular
- study site

Rationale for stratification: The younger age group, including neonates (<28days) and young infants up to 6 weeks of age (<42d) represents the highest surgical risk for many procedures. The pilot study demonstrated an increased effect size in the <6 week age group. Cardiac physiology (uni- versus biventricular) is a major determinant of surgical complexity, risk, and outcome. Less than 10% of CPB procedures are performed in infants 28d to <42d, however the proportion of high-risk procedures in this age group is higher compared to older children. For this reason, we will stratify to < 6 weeks and > 6 weeks of age.

## 7 STUDY PROCEDURE

### 7.1 Screening

All patients undergoing either elective or emergency cardiac surgery will be screened for eligibility criteria. This will be achieved by the on call cardiac surgical team, perfusionist, and PICU study team members.

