#### 5.1.2 Exclusion criteria

- Signs of persistently elevated pulmonary vascular resistance preoperatively requiring iNO or preoperative intravenous use of drugs involved in the NO pathway such as GTN, within 48 hours prior to CPB (oral sildenafil treatment alone is not an exclusion).
- Patient is on ECLS immediately prior to surgery

- Chronic ventilator dependency
- Concurrent known confirmed bacterial sepsis/septic shock, diagnosed within <48 hours prior to surgery and being actively treated with antibiotics at time of surgery (suspected sepsis treated with antibiotics is not an exclusion criteria unless inotropes are required for treatment of septic shock at time of surgery)
- Preoperative acute respiratory distress syndrome requiring HFOV ventilation <48 hours of surgery
- Patient requires high doses of vasoactive drugs prior to surgery with an inotrope score  $\geq 15$  met within 24 hours prior to surgery: Inotrope requirement will be calculated by means of the Vasoactive-Inotrope Score (VIS) (2):  $VIS = \text{dopamine dose (mcg/kg/min)} + \text{dobutamine dose (mcg/kg/min)} + 100 \times \text{adrenaline dose (mcg/kg/min)} + 100 \times \text{noradrenaline dose (mcg/kg/min)} + 10 \times \text{milrinone dose (mcg/kg/min)} + 10,000 \times \text{vasopressin dose (U/kg/min)}$ .
- Cardiac arrest within one week (7d) prior to surgery
- Emergency cardiac surgery which may preclude obtaining informed consent (defined as acutely required life-saving procedure in a patient unlikely to survive the next hours without the surgery)
- Pre-existing methaemoglobinemia (MetHb > 3%)

NB. Patients that were previously enrolled and randomised into the study with surgical procedure performed that required use of cardio-pulmonary bypass will not get re-randomised. Previously enrolled and randomised patients will undergo the same treatment allocation for subsequent surgeries, unless parents opt out. Rationale: For patients undergoing same procedures, any potentially additive protective impact of NO during CPB on long-term neurodevelopment may become diluted by use of CPB without NO during subsequent procedures. We expect that ca. 10% of all CPB cases <2 years may require subsequent CPB <2 years of age.

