## **6 INTERVENTION**

## 6.1 Treatment arms

Patients allocated to the study gas arm will receive NO, which will be blended into the fresh gas flow kept at 3L/min for the CPB oxygenator with NO levels maintained at 20 ppm via an Ikaria INOmax DSIR (Ikaria, NJ, USA) or similar device. Continuous sampling of NO and NO2 concentration will be undertaken from an access port just prior to the oxygenator. NO will be started immediately when the patient is on CPB and ceased once coming off CPB at the completion of MUFing. Patients allocated to the Placebo arm will receive standard respiratory gases (oxygen-air mix) during bypass at a flow rate of 3L/min. Partial pressures of CO2 will be maintained constantly in both study arms as per the institutional practice.

*Note:* If patients require several CPB runs during the same procedure, the treatment has to be provided for each run using the same treatment allocation for every run (i.e. patients allocated to study gas arm will receive NO at 20ppm for every run).

**Subsequent CPB procedures:** Patients that were previously enrolled and randomised into the study with surgical procedure performed that required use of cardio-pulmonary bypass will not get re-randomised. Previously enrolled and randomised patients will undergo the same treatment allocation for subsequent surgeries, unless parents opt out. The study perfusionists at each study site have access to the treatment allocation, which will remain blinded for all other study team members.

**Blinding arrangements.** Of the investigating team, only the study perfusionist will be aware of the randomisation and NO delivery. Blinding arrangements in the operating theatre will be achieved by covering the NO delivery system with drapes. The dedicated study NO delivery system will be connected to the CPB oxygenator at all times, independent of randomisation. The surgeons, anaesthetists and ICU staff will be not aware which treatment arm a patient been allocated to. The perfusionists will be advised that all aspects of CPB except for provision of NO (or not) should be performed in a standard fashion for study participants. The perfusionist does not attend the surgical handover in PICU. The Data Safety Monitoring Board will be unblinded in the event of a severe adverse event. In our pilot study and the previous published study by Checcia, methaemoglobin values using NO at 20 ppm were similar in both the control and intervention groups (1.4%) [29].

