## **Randomisation**

Randomisation is conducted online through the purpose-built REDCap electronic data capture tool hosted at The University of Queensland (14, 15); the randomisation module can only be accessed by the central study coordinator and the site perfusionist, and only after a patient has been screened, is deemed to have met eligibility criteria and has provided informed consent. A randomisation sequence using variable block randomisation with a 1:1 ratio was generated and loaded into REDCap prior to screening of the first patient. Randomisation is stratified on age (<six weeks, ≥six weeks), cardiac physiology (univentricular, biventricular) and study site. The precise time of randomisation occurs variably prior to starting CPB dependent on site logistics, and the intervention begins with start of CPB.

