## **Statistical analysis**

### *Statistical analysis principles*

- Analyses will be conducted based on the intention-to-treat principle. Specifically, patients who are eligible, who do not meet any exclusion criteria and who undergo randomisation will be analysed based on the treatment group they were allocated to, independent of the compliance with the treatment delivered.
- Participants who had more than one surgery before their second birthday will only have data related to their first surgery for which study consent was available analysed.
- Statistical tests will be two-sided applying a statistical significance level of 0.05. As we are not correcting for multiplicity when comparing secondary or other outcomes, such results will be considered exploratory and will be reported as point estimates with 95% confidence intervals (CIs).
- If there is missing data for the primary outcome measure for any participants, imputation methods will be used.
- Continuous variables will be assessed for normality; this will be undertaken using visual inspection of histograms and Q-Q plots.
- Standard descriptive statistics will be used when summarising variables; frequencies (percentages) for discrete variables, mean and standard deviation (SD) for continuous

variables, or, if continuous variables are non-normally distributed, median with interquartile range (IQR).

- This analysis plan and the primary manuscript will only include analyses up to 28 days. We will present analyses of postoperative delirium, health care costs, inflammatory markers and long-term outcomes (12 months and later post procedure) separately.
- Pre-planned subgroup analyses will be performed including the pre-defined study strata; these will be executed regardless of any potential treatment effect on the primary or secondary outcomes in the main cohort.
- To ensure transparency and reproducibility, the Stata code that will be used to analyse the final study data is available on GitHub (16).
- The trial statistician will be blinded to the treatment group until the analyses outlined in this SAP have been completed.
- Changes in the analysis plan by the investigators effective after publication of this SAP will be declared as such.

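### The SAP's intention-to-treat set drops randomised children found ineligible, and nothing says that judgement is made blind to arm; a smaller opening is that the perfusionist, who has access to allocations, also screens

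*Combined protocol and SAP*

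**What the plan says.** **Analysis set.** The SAP's Statistical analysis principles define intention-to-treat with a condition: "patients who are eligible, who do not meet any exclusion criteria and who undergo randomisation will be analysed" by allocated group. Datasets analysed applies the same restriction to everything except the CONSORT flow diagram. Protocol 11.1 places all analyses under intention-to-treat and attaches no eligibility condition. The protocol's section on withdrawal allows an investigator to withdraw a child who develops an exclusion condition during the study, but keeps results obtained before withdrawal unless consent to data use is revoked.

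**Timing.** Under the SAP's Randomisation section the module is opened "only after a patient has been screened, is deemed to have met eligibility criteria and has provided informed consent". The same section says that the interval from randomisation to bypass varies with site logistics and that treatment starts with bypass. In protocol 5.1.2 the window for inhaled NO or intravenous NO-pathway drugs is "within 48 hours prior to CPB". The sepsis, HFOV and inotrope-score windows (48, 48 and 24 hours) are tied to surgery.

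**Roles.** Protocol 7.1 says of screening: "This will be achieved by the on call cardiac surgical team, perfusionist, and PICU study team members". Protocol 6.1 says: "The study perfusionists at each study site have access to the treatment allocation, which will remain blinded for all other study team members". The SAP adds that "the randomisation module can only be accessed by the central study coordinator and the site perfusionist".

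**The concern.** If ineligible children can leave the analysis after allocation, the comparison is protected only when the decision to remove them is independent of arm and outcome. The plan does not secure this. It names no decision-maker, no blinding requirement, no deadline, and no limit to facts recorded before randomisation. The set is still called intention-to-treat, so a reader of the results would assume that no such removal took place.

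The stakes are raised by the endpoint. Death scores zero ventilator-free days, and several exclusion criteria mark severe illness. A few very sick children removed from one arm could therefore move the estimate, and the planned effect is only 0.2 SD.

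The second opening comes before randomisation. The site role with access to earlier allocations is also among those who screen. With blocked allocation inside small strata, past allocations help to predict the next one. Blinding surgeons and intensive care staff does not close this route.

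**Working it through.** **Step 1: the plan's sample size, used as the base.** Inputs from protocol 11.2: effect 0.2 SD, two-sided alpha 0.05, power 90%, 10% withdrawals, 15% for non-normality. Per arm, n = 2 × ((1.960 + 1.282)/0.2)² = 525.4, so 526. Inflating gives:
- 526 × 1.15/0.90: total 1,346
- 526 × 1.15 × 1.10: total 1,332
- 526 × 1.25: total 1,316

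All are within 3% of the stated 1,320 (660 per arm), which is not in dispute.

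**Step 2: does the text remove ineligible children?** The two SAP sections say the same thing, so the condition is not a slip in one sentence. Under both, a randomised child found to meet an exclusion falls outside every analysis except the flow diagram. Under protocol 11.1 that child stays in. The documents conflict.

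**Step 3: can ineligibility surface after allocation?** Yes. The windows end at surgery or bypass, while randomisation comes earlier by an unstated interval. Source verification, which comes later, could also uncover it.

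**Step 4: what removal from one arm could do.** Assume a fraction f of one arm is removed, lying k SD below the mean, with none removed from the other arm. Then:
- bias = f × k/(1 − f)
- SE = √(1/660 + 1/(660(1 − f)))
- type I error = 1 − Φ(1.96 − bias/SE) + Φ(−1.96 − bias/SE)

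Both f and k are assumptions; the documents give neither.

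| f | children | k = 1: bias (SD), type I | k = 2: bias (SD), type I |
|---|---|---|---|
| 0.5% | about 3 | 0.005, 5.1% | 0.010, 5.4% |
| 1% | about 7 | 0.010, 5.4% | 0.020, 6.5% |
| 2% | about 13 | 0.020, 6.6% | 0.041, 11.4% |
| 5% | 33 | 0.053, 15.7% | 0.105, 47.1% |

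For example, with f = 0.02 and k = 2: 0.02 × 2/0.98 = 0.041; SE = 0.0553; ratio 0.74; type I error 11.4%. Equal removal from both arms would have little effect.

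**Step 5: predictability at screening.** Strata: 2 age groups × 2 physiologies × 6 sites = 24 cells, or 1,320/24 = 55 children on average. The SAP says only that blocks vary in size. For assumed mixes, a simulated guesser who knows the stratum's whole history and the set of block sizes is right with probability c:
- blocks 2/4: 71.8%
- 2/4/6: 69.7%
- 4/6: 68.9%
- 4/6/8: 67.8%
- 4/8: 67.5%

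Between 2% and 11% of allocations are known with certainty. If screening moved mean prognosis by ±η SD according to the guess, bias = 2η(2c − 1), with SE = √(2/660) = 0.055:
- η = 0.02: 0.014 to 0.017 SD, type I error about 6%
- η = 0.05: 0.035 to 0.044 SD, about 10% to 13%
- η = 0.10: 0.070 to 0.087 SD, about 25% to 35%

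The documents give no value for η. Steps 4 and 5 use a normal approximation on the SD scale, so they illustrate the planned rank and quantile analyses only roughly.

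**The case against.** The case against has real weight. Treatment starts with bypass, so a condition arising between randomisation and bypass cannot be an effect of bypass NO. Dropping such children on facts fixed before treatment, judged blind, would not bias the comparison. Eligibility data for every enrolled child are source-verified, in Australia and New Zealand by a co-ordinator from another site and in the Netherlands by an external company. Protocol 6.1 keeps allocation from all other study team members, and the SAP keeps the trial statistician blinded until its analyses are complete. An exclusion found by those routes would probably be blind. All this stands, but the SAP does not confine removals to those routes or to pre-randomisation facts.

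On screening, the task is shared with two other groups, consent runs through surgeons and research staff, and eligibility is settled before the module opens. At that stage the perfusionist can act only on a predicted arm. Most criteria are objective: the inotrope exclusion is a computed score of at least 15, the emergency exclusion is defined, and methaemoglobin has a numeric limit. Chronic ventilator dependency is left undefined. One gap remains: children screened out are verified only by sample (5% per site in protocol 7.6, 20 per site in the SAP).

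Two stronger readings are tempting. A reader might infer that the perfusionist decides eligibility or can strike out a randomised child; no section gives that role either power alone. A reader might also assume a steered share, say 5% of 1,320 = 66 children chosen with foreknowledge. The 5% has no source, and a guess that is right about 68% to 72% of the time under assumed block sizes is not foreknowledge.

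**Conclusion.** The point holds in two parts of unequal weight. The main part is a conflict between the documents: the SAP's intention-to-treat set excludes randomised children found ineligible, the protocol's does not, and the SAP leaves the decision without a named or blinded judge. Exclusion after allocation could therefore depend on arm. The lesser part is that a role with access to allocations also helps to screen.

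The documents show an opening, not that it was used, and the size of any bias cannot be derived from them. On the assumed values, lopsided removal of a handful of children does little harm, while 2% to 5% of one arm could matter if those children were very sick. This rests on reading the SAP's population definition literally, since no separate procedure for removing ineligible children is described.

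**What to change.** **SAP.** In Statistical analysis principles, delete the two eligibility clauses at the start of the definition; in Datasets analysed, delete the word eligible. Analyse every randomised child in the allocated arm, subject to the existing rule on consent for data use. List children later found ineligible by arm, with the reason. Any analysis that leaves them out is a sensitivity analysis only, based on facts from before randomisation and judged blind to arm. Declare the change, as the SAP already requires for changes after its publication.

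**Protocol 7.1.** For children still to be enrolled, have the surgical or PICU study team members already listed confirm eligibility before the perfusionist opens the randomisation module. The SAP reports that interim analyses at 660 and 1,000 patients have been done, so this can reach at most about 1,320 − 1,000 = 320 children. The SAP change covers everyone randomised.

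**Cost.** A few lines of text, slight dilution from a few ineligible children kept in the primary set, and a small shift of screening work to the other listed staff. The sample size stays at 1,320.

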### 7.2 Data Collection

Baseline variables, primary end points, secondary end points, pre-determined physiological variables of interest, and process of care measures will be prospectively recorded into a study REDCap online database.

**Time Points for Data Collection.** All physiological and blood parameters are captured for the first 48 hours post operatively and analysed (for patients discharged earlier only data up to discharge will be collected). The specific time points for these parameters will be: on admission to PICU (within the 1st hour), 6 hours, 12, 24, 36 and 48 hours post admission (or until PICU discharge). Gross functional performance assessment will be recorded on admission to PICU and upon discharge from PICU and discharge from hospital. Follow-up to define neurological/functional outcome and quality of life (including phone interviews with parents/caregivers) will be performed at 6-12 months postoperatively.

### **Measured Parameters.**

**Baseline variables:** Sex, age, weight, primary cardiac diagnosis, secondary diagnoses including comorbidities (prematurity, syndrome), pre-operative disease severity (pre-operative PICU admission and length of PICU admission, ventilation and length of preoperative invasive ventilation, inotrope use and dose, prostaglandin use pre-op, diuretics, afterload reduction, infection pre-bypass). Functional assessment at baseline pre-surgery using parental interview/questionnaire to define POPC. Pre-operative medications: steroids, antibiotics, inotropes, prostaglandin, afterload reducing agents.

**Surgical intervention and bypass:** Data on performed cardiac surgical procedure, RACHS and Aristotle score (scores describing the complexity of the surgical procedure), amount and type of fluids and blood products given during surgery, length of CPB (for every run if several runs during one surgery are required), aortic cross clamp time, deep hypothermic arrest (temperature, duration), and length of NO or control delivery. Steroids given during theatre. Modified ultrafiltration. MetHb, NO.

**Postoperative status:** Data on postoperative cardiovascular status, respiratory status, urine output will be collected. Arterial and central venous (taken from jugular, subclavian, or femoral central venous catheter) blood gas analysis including lactate measurements. Laboratory tests to define organ dysfunction platelets, white cell count, haemoglobin, creatinine, base excess, pH, pCO2, pO2, SataO2, and coagulation. Amount and type of blood products given during first 24 and 48 hours. Amount of fluid given during first 24 and 48 hours. Delayed chest closure and time to chest closure. Arrhythmia (JET, etc). Intravenous steroids given during 48 hours postoperatively. Use of iNO. MetHb. Delirium. Total inotrope hours, post-operative infections, re-intubations, cardiopulmonary resuscitation, necrotising enterocolitis, readmissions to PICU and child status will be collected at 28 days. In the event that the child has been transferred to another healthcare facility, parents are asked to consider permission to access medical records within the consenting process.

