Children post bypass commonly develop a low cardiac output syndrome (LCOS) which may be life

threatening and represents the major determinant of postoperative outcomes. LCOS manifests with severe organ dysfunction such as respiratory and renal failure, and can lead to organ and brain hypoperfusion, cardiac arrest, and death. The severity of the LOCS is influenced as well by the type of surgery performed, pre surgical condition of the patient and strongly dependent on non-surgical injury of the heart muscle due to CPB. Several studies have shown that postoperative morbidity and mortality are strongly determined by LCOS (Table 1), which is present in ca. 25-40% of children post CPB in the hours immediately following heart surgery [7]. LCOS may lead to a transient or permanent organ damage, brain ischemia, cardiac arrest and death. ***[name]-term outcome may be affected by acute injury of the developing brain caused by brain ischemia during LCOS*** [8].

CPB-related injuries are most pronounced in infants and young children for several reasons, including higher metabolic rate, stronger inflammatory response, higher bypass circuit to patient blood volume, and altered homeostasis. At the same time this is the cardiac surgical group with highest mortality, and with the highest risk of long-term neurological sequelae due to the vulnerability of the immature developing brain. In addition, bypass-induced modulation of inflammatory cytokines can lead to subsequent immunoparalysis enhancing the risk of postoperative invasive infections [9]. Should LCOS become apparent, the level of support that the newly operated on heart receives is increased using fluid boluses and inotropes. Organ replacement such as renal dialysis and prolonged mechanical ventilation may be required. In the most severe cases, the heart is supported mechanically with extracorporeal life support (ECLS). Considering the severe impact of LCOS on patient centered outcomes after surgery for congenital heart disease in children, improved strategies targeting LCOS are urgently needed[8]. Interventions leading to reduced LCOS have a high likelihood to lead to a reduction in the incidence of organ failure, reduce the severe major events such as need for mechanical support of the heart with ECLS, and shorten postoperative ventilation and ICU length of stay.

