***The proposed physiological effect of Nitric Oxide (NO).*** Nitric oxide (NO) is an endogenous anti-inflammatory mediator, with direct protective actions on the endothelial bed and on immunologically active cells. NO has been shown to have a myocardial protective effect, through a reduction of reperfusion injury [17]. NO generation is essential to regulate endothelial function and microvascular inflammation, and dysregulation of endogenous NO during CPB may aggravate the subsequent inflammatory response [18]. Several animal and human studies have demonstrated that exogenous NO can reduce myocardial damage after clinical and experimental settings of ischemia and arrest [19-22]. Reduced nitric oxide (NO) signalling is associated with several known risk factors for the most common cardiovascular diseases (CVDs) [23]. Organic nitrates, such as nitroglycerin (also known as glyceryl trinitrate), have been used clinically in the treatment of CVDs for more than 150 years, but it was only in the late 1970s that their beneficial effects were shown to be due to the release of NO [24, 25]. NO has since been found to be produced endogenously and to have a key role in the regulation of many physiological processes, including cardiovascular function [3]. Together, these findings have triggered substantial interest in the identification of ways to therapeutically modulate NO signalling. Only a few drug candidates designed to directly activate NO signalling have reached the clinic, the most notable of these being inhaled NO for the treatment of newborns with pulmonary arterial hypertension (PAH) [26] and phosphodiesterase (PDE) inhibitors to treat erectile dysfunction [27]. Therapeutic modulation of NO signalling is challenging, as the effect must occur at the correct location, time and dose. These pharmacokinetic characteristics have been an ***advantage in the use of inhaled NO with minimal systemic side effects*** [26]. Inhaled nitric oxide reaches the huge surface of the pulmonary vascular bed, which represents the most powerful endothelial organ in humans. Nitric oxide, when administered as an inhaled gas to adults undergoing cardiac surgery on CPB, was able to blunt the release of markers of myocardial injury and to antagonize the left ventricular subclinical dysfunction during and immediately after cardiopulmonary bypass [28]. Directed delivery of NO to CPB may have therefore have the capacity to reduce the CPB-induced systemic inflammatory response more selectively, with minimal systemic side effects due to the short half life and localized delivery of the gaseous drug, resulting in mitigation of the detrimental consequences of CPB to the host. A previous small single centre U.S. study has tested this hypothesis and reported a reduction in bypass-induced inflammation using the delivery of gaseous nitric oxide (NO) to bypass circuits [29]. Children receiving gaseous nitric oxide into CPB had a significantly shortened duration of mechanical ventilation (8.4 versus 16.3 hours;  $P < .05$ ) and intensive care unit length of stay (53.8 versus 79.4 hours;  $P < .05$ ) compared with the placebo group. The patients had significantly lower troponin and B-type natriuretic peptide levels postoperatively. In addition, patients treated with NO had a less positive fluid balance, with significantly less diuretic usage, and higher haemoglobin levels postoperatively. This study had important limitations, principally the

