## 8 ADVERSE EVENTS AND RISKS

### 8.1 Definitions

Adverse Event (AE) is any untoward medical occurrence in a patient enrolled into this study regardless of its causal relationship to study treatment intraoperatively and ***within the first 48 hours postoperatively.***

Serious Adverse Event (SAE) is any AE that results in:

- Death
- Is life-threatening
- Requires prolongation of existing hospitalisation
- Results in persistent or significant disability/incapacity
- Requires intervention to prevent permanent impairment or damage

**Specific AEs related to NO delivery during CBP: air embolism, severe hypotension during bypass and increased MethHb (MethHb is >3%).** For the purposes of this study the site investigator is responsible for recording all AEs, regardless of their relationship to study intervention, for the period from randomisation until completion of each individual child's participation in the study.

This study is performed in infants and children undergoing high risk cardiac surgical procedures with death or high risk organ support such as ECLS or renal replacement therapy within the expected outcome. We will report all SAE including deaths and the investigators will give clinical recommendations if the death was unexpected and reason for further investigation by the DSMB.

Additional screening for adverse events will occur at the time of patient discharge from hospital.

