#### *Safety outcomes*

Adverse drug reactions considered to be possibly, probably, or definitively related to the study treatment based on the judgement of the treating local physician, will be reported in supplementary material. Additionally, the proportion of patients with at least one adverse event will be compared between the two treatment groups using logistic regression as described above for secondary outcomes.

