#### **List of planned supplementary material**

- Funding sources
- Trial committee and NITRIC trial investigators
- Data and Safety Monitoring Board Terms of Reference
- Data and Auditing Monitoring Plan
- Enrolment statistics by site and country
- List of congenital heart disease conditions and surgeries
- List of protocol violations
- Results of interim analyses
- Consent details
- Volume of blood product transfused between study arms
- Listing of adverse events
- Kaplan-Meier survival curves for length of PICU stay and length of hospital stay
- Results of subgroup analyses
- Forest plot of the treatment effect across subgroups for the primary and secondary outcomes.
- Results of sensitivity analyses

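### Postoperative infection, cardiopulmonary resuscitation and necrotising enterocolitis are collected at 28 days, but no event-specific comparison between arms is planned

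*Combined protocol and SAP*

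**What the plan says.** Protocol 7.2, under postoperative status in Measured Parameters: "Total inotrope hours, post-operative infections, re-intubations, cardiopulmonary resuscitation, necrotising enterocolitis, readmissions to PICU and child status will be collected at 28 days".

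The background (protocol 2.1) gives reasons to look at these events. It says that "bypass-induced modulation of inflammatory cytokines can lead to subsequent immunoparalysis enhancing the risk of postoperative invasive infections", and that "Nitric oxide (NO) is an endogenous anti-inflammatory mediator, with direct protective actions on the endothelial bed and on immunologically active cells". It also names cardiac arrest as a possible result of low cardiac output syndrome, which the intervention is meant to reduce.

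For harm, SAP Safety outcomes plans two things. The first is a supplementary report of "Adverse drug reactions considered to be possibly, probably, or definitively related to the study treatment based on the judgement of the treating local physician". The second is a comparison in which "the proportion of patients with at least one adverse event will be compared between the two treatment groups using logistic regression". The SAP's supplementary list adds "Listing of adverse events", and protocol 8.1 promises that all serious adverse events will be reported.

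Protocol 8.1 defines an adverse event as one occurring during surgery or "within the first 48 hours postoperatively". The same section, and 8.3, have adverse events recorded from randomisation to the end of the child's participation.

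**The concern.** The three events are serious, already collected, and tied by the protocol's own rationale to the pathways the treatment acts on. Yet the plan produces no count by arm, no effect estimate and no confidence interval for any of them. The one between-arm safety comparison gives a minor event the same weight as an arrest, and the related-reaction report depends on the local physician attributing the event to the study gas. Infection, arrest and enterocolitis after heart surgery in infants can readily be put down to the operation or the underlying disease.

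At stake is what the 28-day report can say about specific harms, or specific benefits, from data the trial already holds. A reader would see the ventilator-free-day and low-cardiac-output results without knowing whether infections or arrests differed between arms.

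**Working it through.** **1. Where the three events appear.**
- Collected: protocol 7.2.
- Not named: protocol 3.2 and 3.3; the Definitions list in 7.2; SAP Outcome measures, Safety outcomes, Table 3, the figure and supplement lists, and S2.
- Not deferred: SAP Statistical analysis principles sends delirium, costs, inflammatory markers and long-term outcomes to separate reports, but not these events. It also limits this SAP to analyses up to 28 days, which is their time frame.

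**2. The plan's own figure.** This point rests on no stated figure, but the sample size sets what a comparison could show. Inputs (protocol 11.2): effect 0.2 SD, power 90%, two-sided 5%, 10% withdrawals, 15% for non-normality.
- n per arm = 2(1.960 + 1.282)² / 0.2² = 526 after rounding up.
- With 25% added: 657.5, so 2 × 658 = 1316.
- With × 1.15 × 1.10: 665.4, so 2 × 666 = 1332.
- With × 1.15 / 0.90: 672.1, so 2 × 673 = 1346.

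The stated 1320 (660 per group) is within 2% of each. After 10% withdrawals, 660 × 0.9 = 594 per arm, or 1188 in all.

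**3. Precision of a direct comparison.** Control rates are assumed. If both arms have rate p, the half-width is 1.96 × √(2p(1−p)/594).
- p = 5%: 1.96 × √(0.095/594) = 2.5 points; about 1188 × 0.05 = 59 events in all.
- p = 10%: 1.96 × √(0.18/594) = 3.4 points; about 119 events.

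**4. Power of a direct comparison.** Power = Φ{[|p2 − p1| − 1.96√(2p̄(1−p̄)/n)] / √[(p1(1−p1) + p2(1−p2))/n]}, where p̄ is the mean of p1 and p2.
- 5% vs 10%, n = 594: (0.05 − 1.96 × 0.01528)/0.01522 = 1.32, power 91% (93% at n = 660).
- 10% vs 15%, n = 594: (0.05 − 1.96 × 0.01919)/0.01914 = 0.65, power 74% (about 79% at n = 660).

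Smallest excess detectable with 80% power:

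| Assumed control rate | 594 per arm | 660 per arm |
|---|---|---|
| 1% | 3.4% (RR 3.4) | 3.2% (RR 3.2) |
| 2% | 5.0% (RR 2.5) | 4.8% (RR 2.4) |
| 5% | 9.2% (RR 1.8) | 8.9% (RR 1.8) |
| 10% | 15.4% (RR 1.5) | 15.1% (RR 1.5) |
| 15% | 21.3% (RR 1.4) | 20.9% (RR 1.4) |

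**5. The same excess inside the pooled comparison.** Let b be the share of patients with some other adverse event, assumed equal in both arms and independent of the event of interest. The any-event rate is 1 − (1−b)(1−p). For 5% vs 10% with 660 per arm, where the direct comparison has 93% power:

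| b | Any-event rates | Power |
|---|---|---|
| 10% | 14.5% vs 19.0% | 59% |
| 20% | 24.0% vs 28.0% | 38% |
| 30% | 33.5% vs 37.0% | 26% |
| 50% | 52.5% vs 55.0% | 15% |

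**6. If only events within 48 hours count.** Replace p by p × s, where s is the share of these events falling in the window (assumed). With b = 20% and 660 per arm, s = 10%, 25% and 50% give 20.4% vs 20.8%, 21% vs 22% and 22% vs 24%. Power is about 4%, 7% and 14%. If the wider recording window applies, step 5 is the relevant one.

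**The case against.** The strongest reply is that harms do have routes into the report. A serious infection, arrest or enterocolitis recorded as an adverse event would be counted in the pooled comparison and listed, and protocol 8.1 promises all serious events. A fatal event enters 28-day death and sets ventilator-free days to zero. One that prolongs support affects ventilation time or length of stay, all reported by arm. This stands. A reader might infer that these harms would go unreported, and the documents do not support that. What is missing is a separate estimate.

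A reader might also infer that nitric oxide is expected to raise infection. No passage says so. Protocol 2.1 links infection to bypass-induced immune disturbance and suggests that nitric oxide may dampen the bypass response with minimal systemic effect, which could equally mean fewer infections. The steroid evidence cited there concerns mortality, general risk and lack of benefit, not infection.

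A third inference is that anything after 48 hours falls outside the adverse event system. The definition in 8.1 reads that way, but the recording instructions in 8.1 and 8.3 run to the end of participation. The documents conflict, so the matter is open.

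Finally, every event rate used here is assumed, and other collected items, such as arrhythmia, are not named as outcomes either. Choosing which items to name is partly judgement. These three have the stronger case because of their seriousness and the protocol's own rationale.

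**Conclusion.** The point holds as a gap in event-specific reporting. An imbalance in infection, resuscitation or necrotising enterocolitis, in either direction, would not be separately estimated. It could be diluted in the pooled comparison: in the 5% versus 10% example, power falls from 93% to between 15% and 59%, on assumed background rates and independence. It might not be counted at all after 48 hours, depending on which adverse event window applies.

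A direct comparison is informative for events at about 5 to 15% (80% power for relative risks of about 1.8 down to 1.4). It does not settle every question: a half-width of 3.4 points cannot exclude a 3-point excess when the observed difference is zero. For events at 1 to 2%, the interval is mainly descriptive. The primary analysis, the sample size and the main secondary outcomes are unaffected. This is a low-cost improvement worth making, not a flaw in the trial's main conclusion.

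**What to change.** 1. In SAP Safety outcomes, and in Table 3 or the supplement, name postoperative infection, cardiopulmonary resuscitation and necrotising enterocolitis, each counted to 28 days from CPB start whether or not it was also recorded as an adverse event. Cite the definitions used in the case report form; the protocol and SAP text gives none.
2. Report n (%) by arm with the odds ratio and 95% CI from the logistic model already specified for binary secondary outcomes (age group and physiology as fixed effects, site as random). Where counts are too small for that model, give n (%) with a risk difference and an exact CI.
3. Label the results exploratory, without multiplicity correction, as the SAP already does for secondary and other outcomes.
4. Reconcile the adverse event definition in protocol 8.1 with the recording periods in 8.1 and 8.3, and state which events enter the pooled comparison.

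The cost is SAP wording, three table rows and a few more exploratory comparisons. The data are already collected. Full source verification is guaranteed only for items behind the primary and secondary outcomes, so the sponsor should also decide whether to extend it to these three.
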